### Study endpoints

The primary endpoint will be the proportion of the population with specific antibodies against SARS-CoV-2.

Secondary endpoints will be as follows:The proportion of the population with specific antibodies against SARS-CoV-2 in each subgroup of age (60 and over, 19–59 years old, teenagers aged 15–18 and those aged 10–14 years) and by gender (males, females).The proportion of asymptomatic infections (presence of antibodies in patients with no clinical signs of SARS-CoV-2 infection) in the population, in each subgroup of age (60 and over, 19–59 years old, teenagers aged 15–18 and those aged 10–14 years) and by gender (males, females).

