### Sample size calculation

Using the sample size calculator available on Openepi [31] (http://www.openepi.com/SampleSize/SSPropor.htm), with an expected SARS-CoV-2 seroprevalence of 10%, an accuracy of ± 3%, an alpha risk = 5% and no design effect (Deff = 1), we need at least 384 persons in each gender and age stratum at the final round (fourth timepoint). This number has been rounded to 452 to account for approximately 85% usable data.

Therefore, considering a non-response rate of 70% at inclusion and 30% between the data collection rounds (one to four), Table 1 (below) gives the number of subjects required per age and gender group per visit. At the final round (fourth timepoint), there should be 452 for each stratum. The details of the sample size calculation are presented in Table 2.

**Table 1 Tab1:** Distribution of the city zones for the socio-anthropological study

	Bobo Dioulasso	Ouagadougou
Residential/central	1	1
Residential /peripheral	1	1
Poorer/central	1	1
Poorer/ peripheral	1	1
Total	4	4

**Table 2 Tab2:** The study sample calculation strategy

Age and gender groups	Average number of people per household	Average number of households per EA* in the study cities	Number of EA needed for the study	Estimated number of people in the selected EA	Estimated number of people to contact	Estimated number of people to select in each EA	Estimated number of people needed after round 1	Estimated number of people needed after round 2	Estimated number of people needed after round 3	Estimated number of people needed after round 4
Men and women aged 60 and over	0.15	220	160	5280	4393	28	1318	922	646	452
Men aged 19 to 59	1.26	220	160	44,352	4393	28	1318	922	646	452
Women aged 19 to 59	1.10	220	160	38,720	4393	28	1318	922	646	452
Teenagers aged 15 to 18	0.51	220	160	17,952	2152	14	0	0	646	452
Teenagers aged 10 to 14	0.61	220	160	21,472	2152	14	0	0	646	452
Total				127,776	17,483	112	3953	2767	3229	2260

*EA** Enumeration Area

To avoid the design effect (Deff = 1) in the calculation of the sample size, the sampling method will be two-stage random sampling with a probability proportional to their size in the resident population according to the data from the National Institute of Statistics and Demography survey (INSD).

To contact the 17,483 people for inclusion we will randomly choose 160 Enumeration Areas (EA) in Ouagadougou and Bobo-Dioulasso. In the two cities together 160 EA out of 1728 will be selected with a probability proportional to their size.

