At the laboratory, plasma samples will be centrifuged and aliquoted within 12 h of the blood collection. If the time to preparation (centrifugation and aliquoting) is likely to exceed 12 h, it will be temporarily stored at + 4 °C for up to a maximum of 72 h. To minimize the number of freeze–thaw cycles [7], two (2) aliquots of 1 ml plasma each will be prepared from each blood sample. One of these will be used for the serological tests by ELISA anti-SARS-CoV-2 for both IgM and IgG. For participants who consent to conservation of their blood samples, the second aliquot will be stored at −80 °C in a secure biobank at the laboratory of the MURAZ center in Bobo-Dioulasso, in case needed for quality control, additional tests or future research.

Laboratory tests will use the WANTAI SARS-CoV-2 Ab ELISA, an Enzyme-Linked Immunosorbent Assay (ELISA) intended for qualitative detection of total antibodies (including IgG and IgM) to SARS-CoV-2 in human serum and Acid Citrate Dextrose (ACD) plasma. The WANTAI SARS-CoV-2 Ab ELISA is intended for use as an aid in identifying individuals with an adaptive immune response to SARS-CoV-2, indicating recent or prior infection. Before being used in this study, the assays will be validated for the Burkinabe context on a small series of characterized samples from Burkinabe patients (10 positive and 10 negative samples by PCR).

The results of the biological analyses and the questionnaire data will be recorded in an electronic case report form (CRF), which will be secured by personal access codes for each researcher. Data will be transferred to the data management center at the MURAZ center daily, after preliminary data checks by the supervisors in the field. Data will be cleaned and tested for coherence and completeness, and aberrant values will be identified. Queries generated in case of aberrant data will be sent to the research supervisors in the field to be resolved by the researchers before the end of data collection.

The database will be locked after the data has been cleaned and all queries have been resolved. The database will then be exported for statistical analysis.

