### Statistical analysis

For the statistical analysis, this research project will adopt a dynamic approach and will constantly integrate latest knowledge emerging about COVID-19. A first analysis will be performed after the first collection on day 0, to enable important information that could be useful for the fight against COVID-19 to be relayed to the authorities in Burkina Faso.

The following analyses will be performed [7]:Calculation of the cumulative incidence by age group: i.e., the proportion of individuals who are seropositive for SARS-CoV-2 infection according to age (60 and over, 19–59 years old, teenagers aged 15–18 and children aged 10–14 years).Calculation of the cumulative incidence by gender: i.e., the proportion of individuals who are seropositive for SARS-CoV-2 infection according to gender (men, women).Serological response to infection (if the serological tests enable us to evaluate this criterion): i.e., the course of serum levels of specific antibodies against SARS-CoV-2 (increase in titers across the different measurement timepoints).Describe and compare individual, socio-economic characteristics, presence of comorbidities and exposure according to serological status of the population.

Quantitative variables will be described as mean ± standard deviation (SD) and median (range) and compared using the Student t or Mann–Whitney U tests as appropriate. Qualitative variables will be described as number and percentage and compared using the chi square or Fisher’s exact test, as appropriate.

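### Phase 1 equates cumulative incidence with the proportion testing positive, its ±3% margin covers sampling error only, and the 10+10 local validation cannot show that the assay is accurate enough for that margin

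*Protocol article*

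**What the plan says.** All references are to the protocol article.

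- **Estimand and estimator.** The objectives at the end of the Background treat cumulative incidence and seroprevalence as the same thing. Phase 1, Statistical analysis, defines cumulative incidence by age group as "the proportion of individuals who are seropositive for SARS-CoV-2 infection according to age", with a parallel definition by gender. Neither place mentions test error.
- **Secondary endpoint.** Phase 1, Study endpoints, defines asymptomatic infection as "presence of antibodies in patients with no clinical signs of SARS-CoV-2 infection".
- **Precision.** Phase 1, Sample size calculation, assumes 10% seroprevalence, a margin of ±3 percentage points, "an alpha risk = 5% and no design effect (Deff = 1", and concludes that "we need at least 384 persons in each gender and age stratum at the final round". This is inflated to 452 for 85% usable data.
- **Assay.** Phase 1, Data collection and management, names a commercial total-antibody ELISA whose positive result is read as "indicating recent or prior infection". Before use it will be "validated for the Burkinabe context on a small series of characterized samples from Burkinabe patients (10 positive and 10 negative samples by PCR". No sensitivity or specificity is given anywhere in the article.

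**The concern.** At a prevalence of 10% or less, about nine in ten people tested have no antibodies to find. A small false-positive rate among them therefore adds a visible number of positives. The Background itself says that general-population seroprevalence in available studies is below 10%.

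If the proportion testing positive is reported as cumulative incidence, it carries a bias that the ±3% interval does not show. The bias goes further than the primary endpoint. A false positive without symptoms meets the definition of an asymptomatic infection, and false positives dilute the planned comparisons by serological status. Day-0 results are to go to the authorities, so the first figure released would carry the same error.

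The natural safeguard is evidence that the assay performs well in this setting. The only such evidence described is a panel of ten positives and ten negatives.

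**Working it through.** **1. The plan's own figure.** Inputs from Phase 1, Sample size calculation: p = 0.10, d = 0.03, two-sided alpha 5%.

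n = 1.96² × 0.10 × 0.90 / 0.03² = 384.1, and 384 / 0.85 = 451.8, rounded to 452. Both stated figures reproduce. The formula contains binomial sampling variance and nothing else, so the planned interval at an observed 10% is 7% to 13% with the test treated as error-free.

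**2. What ten samples can show.** If all ten negatives test negative, the exact (Clopper-Pearson) two-sided 95% lower limit for specificity is 0.025^(1/10) = 0.69. The same limit applies to sensitivity from ten positives. The chance that a test with specificity Sp passes 10/10 is Sp¹⁰:

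- Sp = 95%: 0.95¹⁰ = 0.60
- Sp = 90%: 0.90¹⁰ = 0.35

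**3. Effect on the estimate.** Apparent prevalence = p × Se + (1 − p)(1 − Sp). False share of positives = (1 − p)(1 − Sp) / apparent prevalence. Sensitivity of 90% is an assumption, because the article gives none.

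| True p | Se (assumed) | Sp (assumed) | Apparent | Bias (points) | False share |
|---|---|---|---|---|---|
| 10% | 90% | 99% | 0.090 + 0.009 = 9.9% | −0.1 | 9% |
| 10% | 90% | 98% | 0.090 + 0.018 = 10.8% | +0.8 | 17% |
| 10% | 90% | 97% | 0.090 + 0.027 = 11.7% | +1.7 | 23% |
| 10% | 90% | 95% | 0.090 + 0.045 = 13.5% | +3.5 | 33% |
| 5% | 90% | 97% | 0.045 + 0.0285 = 7.35% | +2.4 | 39% |

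**4. Where the bias equals the margin.** With Se = 90%, solving 0.09 + 0.9(1 − Sp) = 0.13 gives Sp = 95.6%. With Se = 100%, 0.9(1 − Sp) = 0.03 gives Sp = 96.7%, and such a test passes 10/10 with probability 0.967¹⁰ ≈ 0.71. Excluding that false-positive rate (3.33%) with no errors seen would take ln(0.025) / ln(1 − 0.0333) = 108.8, about 109 known negatives at two-sided 95%.

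**5. Whether the panel could supply the correction.** The Rogan-Gladen estimate is (apparent + Sp − 1) / (Se + Sp − 1). For an observed 10% of 384, taking Se and Sp from a perfect 10/10 on each side (Jeffreys priors), the simulated 95% interval is about 0% to 13%, against the planned 7% to 13%. The panel is too small to serve as the source of a correction.

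**The case against.** Several points on the other side are fair.

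- **Adjustment may be planned elsewhere.** This is a condensed article. It says that Phase 1 follows a WHO protocol and will take up new knowledge as it emerges, and it never uses the word "raw". A missing adjustment formula would not be a finding by itself. What remains is that the estimator is stated, the margin is stated, and neither allows for test error.
- **The panel need not be the only source of performance data.** A reader might infer that test error as large as ±3% can be neither excluded nor corrected. The article does not support that. It does not say that the 20 samples are the sole basis for sensitivity and specificity, and calling them a small series reads like local verification of a commercial kit. Correction with external figures is possible. The 69% limit describes the panel, not all that is known of the assay.
- **The bias may be modest.** With 90% sensitivity and 10% prevalence it reaches 3 points only at about 95.6% specificity or lower. At 99% the two errors nearly cancel. Actual specificity may be high.
- **PCR as reference.** A reader might infer that PCR-negative samples would hide a poor test. The effect goes the other way: a PCR-negative person with antibodies from past infection makes specificity look worse, and a PCR-positive person sampled before seroconversion makes sensitivity look worse. The article calls the samples characterized and does not give their timing. PCR status is an imperfect reference for past infection, but it does not conceal false positives.

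None of this makes ten negatives sufficient for a ±3% target, or adds test error to the stated interval.

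**Conclusion.** The point holds in a limited form. The stated estimator is the proportion testing positive, the stated margin covers sampling error alone, and the only validation described cannot show performance good enough for that margin.

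Under assumed 90% sensitivity and 10% true prevalence, the bias is +0.8 points at 98% specificity, +1.7 at 97% and +3.5 at 95%, with 17% to 33% of positives false. At 5% true prevalence and 97% specificity, 39% of positives are false. These sizes depend on assumed assay performance, since the article gives none. The limits of a ten-sample panel do not depend on that assumption.

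It does not follow that the assay is poor or that the error is beyond correction.

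**What to change.** - Report a test-adjusted seroprevalence (Rogan-Gladen or a Bayesian equivalent) beside the raw proportion, overall and by stratum. Take sensitivity and specificity from external evaluations and carry their uncertainty into the interval.
- Add a sensitivity table over specificity, for example 95% to 99.5%. For an observed 10% with sensitivity 90%, the adjusted value is 0.050/0.850 = 5.9% at 95%, 0.070/0.870 = 8.0% at 97%, 0.080/0.880 = 9.1% at 98% and 0.095/0.895 = 10.6% at 99.5%.
- Apply the same adjustment and table to the asymptomatic proportion.
- Describe the 10+10 run as a bench check and not as the source of the correction.
- Where stored pre-epidemic negatives and convalescent positives are already available, prefer them to PCR-negative and acute PCR-positive patients. The article does not show that such samples exist, and a better-sourced panel of ten would still be a panel of ten.

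The cost is analysis wording, wider intervals and reliance on outside performance figures. Even with sensitivity 90% and specificity 97% known exactly, the half-width at an observed 10% grows from 3.0 to 3.0/0.87 = 3.4 points. The external figures should also match the specimen used: the article describes the kit for serum and ACD plasma, while blood is drawn into EDTA tubes. Participant numbers and field procedures need not change.

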### Statistical analysis

For the statistical analysis, this research project will adopt a dynamic approach and will constantly integrate latest knowledge emerging about COVID-19. A first analysis will be performed after the first collection on day 0, to enable important information that could be useful for the fight against COVID-19 to be relayed to the authorities in Burkina Faso.

The following analyses will be performed [7]:Calculation of the cumulative incidence by age group: i.e., the proportion of individuals who are seropositive for SARS-CoV-2 infection according to age (60 and over, 19–59 years old, teenagers aged 15–18 and children aged 10–14 years).Calculation of the cumulative incidence by gender: i.e., the proportion of individuals who are seropositive for SARS-CoV-2 infection according to gender (men, women).Serological response to infection (if the serological tests enable us to evaluate this criterion): i.e., the course of serum levels of specific antibodies against SARS-CoV-2 (increase in titers across the different measurement timepoints).Describe and compare individual, socio-economic characteristics, presence of comorbidities and exposure according to serological status of the population.

Quantitative variables will be described as mean ± standard deviation (SD) and median (range) and compared using the Student t or Mann–Whitney U tests as appropriate. Qualitative variables will be described as number and percentage and compared using the chi square or Fisher’s exact test, as appropriate.

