Firstly, current techniques for COVID-19 diagnosis are expensive (e.g., PCR, for detection of genetic material from the virus) [20, 21], limiting the number of analyses that can be performed. This makes it difficult, not to say impossible to estimate the actual number of persons infected by the virus in the general population of Burkina Faso. Furthermore, the full spectrum of disease, and the relative proportions of benign or asymptomatic cases not requiring medical care, remain unclear [22]. As in many low- and middle-income countries, in Burkina Faso, the management of the pandemic has concentrated primarily on patients presenting with severe forms of disease. Although recommended by the WHO, few countries have assessed seroprevalence at the population level. According to available studies, seroprevalence for SARS-CoV-2 infection among the general population remains low (below 10%) [22] and reports mainly stem from western countries. In this context, in Burkina Faso, and in Africa in general, there remains some uncertainty as to the principal epidemiological and serological features of this novel pathogen, in particular its capacity to spread among the population, and its virulence. Yet, surveillance of seropositivity for IgG and IgM antibodies [23, 24] would make it possible to detect the spread of infection and estimate the cumulative incidence in the population [22]. It would also give insights during the pandemic into the proportion of the population already exposed to the virus, and thus, potentially immunized.

To the best of our knowledge, scores to predict patients at risk of severe forms of disease, or death, from among those with COVID-19 are not currently available in Burkina Faso or other countries with limited resources. Such scores would make it possible to focus preventive strategies and available resources on this high-risk sector of the population. Such scores might also contribute to reducing the costs associated with management of COVID-19 patients in a country where resources are scarce. To date, few studies have investigated the creation of a score or algorithm for predicting the occurrence of severe complications in patients with COVID-19 [25, 26], especially in African populations where the incidence rate and mortality are lower than the alarmist forecasts of international health authorities at the beginning of the pandemic.

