Finally, preventive strategies against COVID-19 were developed and rapidly disseminated to the Burkinabe population by the media, associations, non-governmental organizations, local elected officials, religious and cultural leaders, and healthcare professionals, without giving a second thought to the acceptability of the measures being promoted for the population. However, the literature as well as media reports indicate that during other epidemics, notably Ebola [27–30], the implementation of preventive strategies (including raising awareness among the population, institutional isolation of infected individuals, collective management of cadavers by specialized healthcare teams) led to misunderstanding and conflictual interpretations between national or international scientific experts, and local populations. This breakdown in communication led to increased mortality, underlining the importance of evaluating the acceptability of preventive strategies for the population in the specific context of Burkina Faso. In addition, several specialists have questioned the feasibility of social distancing and isolation of suspected infected individuals in African populations where the community-based culture prevails. There are also unanswered questions regarding the pathways of care, patient management, and patients’ experiences. The specific objectives of this project comprise three phases, namely:To determine cumulative incidence (i.e., seroprevalence) of SARS-CoV-2 infection in the Burkinabe population (phase 1: sero-epidemiological study);To identify the predictors of the occurrence of severe complications and to identify the prognostic factors for mortality (phase 2: clinical epidemiology);To analyze the healthcare pathways and patient experiences of management of COVID-19 in healthcare centers dedicated to SARS-CoV-2 infected patients, and to explore the perceptions, acceptability, and application of preventive strategies among the population (phase 3: socio-anthropological study).

Embracing all these problems, we developed the present project, whose overarching aim is to generate novel, pragmatic epidemiological and socio-anthropological data using robust scientific methods, to support Burkina Faso and guide policy in its fight against the COVID-19 pandemic.

To the best of our knowledge, this will be one of the first studies of this type to be performed in Sub-Saharan Africa since the emergence of COVID-19.

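### Phase 1 takes the proportion testing positive as cumulative incidence, with no stated correction for assay sensitivity and specificity, so the estimate can be biased in either direction by an amount the protocol does not bound

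*Protocol article*

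**What the plan says.** All of this is in the protocol article.

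- **Objective** (Background): "To determine cumulative incidence (i.e., seroprevalence) of SARS-CoV-2 infection in the Burkinabe population". The two terms are treated as the same quantity.
- **Estimator** (Phase 1, Statistical analysis): cumulative incidence by age is "the proportion of individuals who are seropositive for SARS-CoV-2 infection according to age". The gender analysis uses the same definition.
- **Endpoints** (Phase 1, Study endpoints): the primary endpoint is the antibody-positive share of the population. A secondary endpoint counts antibody-positive people without clinical signs as asymptomatic infections.
- **Expected level**: the Phase 1 sample size is worked out "with an expected SARS-CoV-2 seroprevalence of 10" per cent, with "an accuracy of ± 3" per cent. The Background puts general-population seroprevalence below 10%.
- **Assay** (Phase 1, Data collection and management): a qualitative total-antibody ELISA. No Se or Sp is given. A check is planned on "10 positive and 10 negative samples by PCR".
- **Use**: a first analysis follows the day 0 collection, to inform the authorities.

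**The concern.** The share testing positive estimates the share infected only if the assay makes no errors or its errors cancel. At a prevalence of 10% or less, at least nine people in ten are truly negative, so a small false-positive rate adds visibly to the count. Missed infections pull the other way. The net bias therefore depends on Se, Sp and the prevalence in each group, and the article gives neither Se nor Sp.

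Three results are exposed:

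- the primary proportion reported to the authorities;
- the age and gender contrasts, which misclassification compresses;
- the asymptomatic proportion, because a false positive without symptoms is counted there directly.

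The ±3 point margin behind the sample size allows for sampling error only.

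**Working it through.** **1. The plan's own figure.** With p = 0.10, d = 0.03 and Deff = 1:

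n = 1.96² × 0.10 × 0.90 / 0.03² = 384.1, and 384 / 0.85 = 451.8.

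The stated 384 and 452 reproduce. The calculation treats the observed proportion as the true one.

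**2. Bias of the raw proportion.** Observed = p × Se + (1 − p) × (1 − Sp). Se and Sp are assumptions. Bias in percentage points at a true 10%:

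| Se | Sp 99.5% | Sp 99% | Sp 98% | Sp 97% | Sp 95% |
|---|---|---|---|---|---|
| 100% | +0.45 | +0.9 | +1.8 | +2.7 | +4.5 |
| 95% | −0.05 | +0.4 | +1.3 | +2.2 | +4.0 |
| 90% | −0.55 | −0.1 | +0.8 | +1.7 | +3.5 |
| 80% | −1.55 | −1.1 | −0.2 | +0.7 | +2.5 |

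A bias of +3 points at 10% needs Sp = 1 − 0.03/0.90 = 96.7% with Se 100%, or 1 − (0.03 + 0.01)/0.90 = 95.6% with Se 90%.

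**3. Range over Se 80–95% and Sp 95–99.5%.** The extremes lie at the corners.

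- True 5%: 0.05 × 0.80 + 0.95 × 0.005 = 4.5%, up to 0.05 × 0.95 + 0.95 × 0.05 = 9.5%.
- True 10%: 0.10 × 0.80 + 0.90 × 0.005 = 8.45% (about 8.5%), up to 0.10 × 0.95 + 0.90 × 0.05 = 14.0%.

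**4. Lower prevalence and contrasts, with Se 90% and Sp 98%.**

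- True 2%: 0.018 + 0.0196 = 3.76%. False positives are 0.0196/0.0376 = 52% of all positives.
- True 5%: 0.045 + 0.019 = 6.4%. False positives are 0.019/0.064 = 30%.
- True 10%: 0.090 + 0.018 = 10.8%.
- Differences between groups are multiplied by Se + Sp − 1 = 0.88. A true ratio of 10% to 2% (5-fold) reads 10.8/3.76 = 2.9-fold.

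**5. Effect on a nominal 95% interval.** At n = 384, true 10% and Se 100%, the actual coverage of a Wald interval is 94% at Sp 100%, 93% at 99%, 83% at 98% and 60% at 96.7%. The pooled estimate is more exposed. Table 2 gives 3,953 people after round 1; unweighted and with Deff = 1, the margin is 1.96 × √(0.10 × 0.90 / 3,953) = ±0.9 points, which is as large as the +0.9 bias at Sp 99% with Se 100%.

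**6. What the 10 + 10 panel can show.** If all 10 negatives test negative, the exact two-sided 95% lower limit for Sp is 0.025^(1/10) = 69%. An assay with Sp 96.7% gives 10 of 10 with probability 0.967^10 = 71%, and one with Sp 99% with probability 0.99^10 = 90%. A clean panel hardly separates the two.

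**7. Cost of correcting.** Rogan-Gladen: (observed + Sp − 1)/(Se + Sp − 1). With Se and Sp taken as known, the half-width is 1.96 × √(a(1 − a)/n)/(Se + Sp − 1), where a is the observed proportion. At true 10%:

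| Se, Sp | a | Margin at n = 384 | Usable results for ±3 points |
|---|---|---|---|
| 95%, 99% | 10.4% | ±3.2 | 451 |
| 95%, 98% | 11.3% | ±3.4 | 495 |
| 90%, 97% | 11.7% | ±3.7 | 583 |

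**The case against.** The strongest reply is that the article never says results will be left unadjusted. Its definitions could be read as naming the target quantity, which a corrected estimator also targets. Adjustment for test performance is a detail that a condensed article may leave to the full protocol or SAP. The Phase 1 text also says the WHO protocol will be followed, and the analysis list cites the same reference. Those sources are not shown, so they may already settle the matter. That stands as a limit on the point. It does not remove it: the article writes out a definition that equates cumulative incidence with the seropositive proportion, and an unseen source cannot be assumed to override it.

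Three stronger readings are tempting, and the documents do not support them.

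- **That the bias is as large as the ±3 point margin.** This needs Sp of about 96–97% or lower, depending on Se, and the article gives no value. At Sp 99% or better the bias at 10% is at most +0.9 points. False positives also act in one direction only, so they are not like for like with a two-sided margin.
- **That false positives always dominate.** At a true 10% with Se 80% and Sp 99%, missed infections remove 2.0 points and false positives add 0.9, so the net is −1.1.
- **That the 10 + 10 panel is meant to supply Se and Sp.** The article presents it as a small local validation and does not link it to the estimator. The fair criticism is only that it cannot bound the bias.

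The article also specifies no analysis interval for Phase 1. The remark about sampling error applies to the sample size margin.

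**Conclusion.** The point holds in a conditional form. As written, the estimator is a biased measure of infection unless assay errors are nil or happen to offset. The direction and size cannot be fixed from the article because Se and Sp are not stated. Under the assumed values, the bias at the expected 10% runs from slightly negative (−0.1 at Se 90%, Sp 99%), through about +1 point (Se 100%, Sp 99%), to +3 points only near Sp 96.7%. Across the wider grid a true 10% reads 8.5–14.0% and a true 5% reads 4.5–9.5%. The relative distortion from false positives is worst in low-prevalence groups: at a true 2% with Se 90% and Sp 98%, about half of the positives are false. Offsetting errors are no safeguard, because the balance shifts with prevalence from group to group. This is a worthwhile and inexpensive improvement to the analysis. It does not invalidate the survey, and it would fall away if the unseen WHO protocol or SAP already prescribes a correction.

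**What to change.** - Report the raw proportion, labelled seropositivity, beside a Rogan-Gladen or Bayesian corrected cumulative incidence, overall and in each age and gender stratum. Do the same in the day 0 report.
- Take Se and Sp from a large, cited evaluation, state its sample sizes, and carry the uncertainty in both into the interval together with sampling error.
- Add a table of corrected estimates over a range of Se and Sp. It is needed partly because published performance may not transfer: Data collection and management describes the assay as intended for serum and ACD plasma but has blood drawn into EDTA tubes.
- Say that the 10 + 10 panel serves only as a local check.
- If the WHO protocol or the SAP already prescribes this, say so in the definition.

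The cost is analysis wording and a little code, with no new visits or participants if a wider margin is accepted. With Se and Sp taken as known, the margin at 384 persons becomes about ±3.2 to ±3.7 points, and uncertainty in Se and Sp widens it further. Holding ±3 points would need 451 to 583 usable results per stratum in the cases shown. The corrected figure also depends on external Se and Sp, which the table makes visible.
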